### Interventions

#### Acupuncture

The acupuncture treatment comprises a standardized combination of points plus additional individual points identified by location (meridian). Table 1 provides a detailed description of the acupuncture points used to allow replication of the intervention. All acupuncture points were selected based on TCM principles, the international literature, and the opinion of national and international experts. In line with the Standards for Reporting Interventions in Clinical Trials of Acupuncture criteria, the treatment was semi-standardized, fulfilling both the requirement of a basic individualized diagnosis and treatment and of a standardized acupuncture treatment for patients with comparable symptoms. In addition to these locations, needles will be inserted into 1–4 *ashi* points (i.e., points where the headache is most painful), if these points are clearly mentioned by the patient during the screening examination.

**Table 1 Tab1:** Acupuncture treatment

Point selection	Pain localization	Acupuncture points	Depth [cun]
Standard		*Baihui* (GV20)	0.5–0.8
		*Taiyang* (EX-HN5)	0.3–0.5
		*Fengchi* (GB20)	0.8–1.2
		*Hegu* (LI4)	0.5–1.0
*Yangming* meridian	Front head, forehead, brow edge	*Neiting* (ST44)	0.5–0.8
		*Yintang* (GV29)	0.3–0.5
*Shaoyang* meridian	Side head, temporal	*Zulinqi* (GB41)	0.3–0.5
		*Waiguan* (SJ5)	0.5–1.0
*Taiyang* meridian	Back head, occipital	*Kunlun* (BL60)	0.5–1.0
		*Houxi* (SI3)	0.5–1.0
*Jueyin* meridian	Top of the head	*Taichong* (LR3)	0.5–0.8
		*Neiguan* (PC6)	0.5–1.0
		*Sishencong* (EX-HN1)	0.5–0.8

The detailed localizations, acupuncture point names, and insertion depths follow the rules of TCM. All acupuncture points will be manually stimulated on needle insertion and before removal of the needle. The *deqi* sensation will be evoked. The needle retention time will be 30 min. Sterile disposable acupuncture needles will be used (25–40 mm × 0.25–0.3 mm; manufacturer: Suzhou Tianxie Acupuncture Instruments Co, or similar). Acupuncture will be used without additional methods, such as moxibustion, cupping or electrical, stimulation, which extend the technique or treatment. Acupuncture will be performed by an experienced acupuncturist with more than 5 years of clinical experience in acupuncture treatment.

#### Medical training therapy

MTT will be provided by experienced and qualified physiotherapists. Based on an initial 45-min physiotherapeutic examination plus a cardiac stress test and testing of strength, endurance, posture control, and flexibility, a training plan will be created. The 12 standardized treatment units will have a duration of 60 min. The intensity will be tailored to the individual patient. A compact self-training program will be handed out, in writing, to the subject so that they can perform the exercises they have learned independently three times a week. Treatment generally adheres to the principles of MTT and comprises a combination of strength training, endurance training, flexibility training (yoga exercises), and posture training with coordinative elements. Table 2 provides a detailed description of the MTT approach used to allow replication of the training program.

**Table 2 Tab2:** Medical training therapy

Method	Intervention	Intensity	Frequency	Duration
Cardiovascular training	Cycling	75% of maximum Heart Rate	1	15 min
	Rowing machine			
	Cross trainer			
	Treadmill			
Strength and endurance training	Pull-down	40% of max. strength	2 × 25	10
	Butterfly reverse			
	Rowing			
Coordinative training	Postural training	Individual level	1	3
Proprioceptive training	Segmental stabilization of the spine in flection and extension		2.5–4.8 Hz	5 × 15 s
	Segmental stabilization of the spine in lateral flexion			
	Reducing muscle tension			
Training to improve mobility and flexibility	Stretching the erector spinae muscles	Individual level	1	30 s
	Stretching the iliopsoas muscle and extending the flank		4 × 1	4 × 20 s
	Spinal mobilization from the quadruped stand		4 × 1	4 × 20 s
	While supine, extension and abdominal respiration, shoulder bridge and candle		2	30 s
	Forearm plank		2 × 1	30 s
	Rotational strain of the spine with breathing recess		5	5 × 10 s
	Stretching the trapezius and pectoralis muscles		2	30 s

#### Combination of acupuncture and MTT

The complex health intervention to be evaluated in the study is the combination of MTT and acupuncture. Following each MTT session and a short rest, the patients will receive acupuncture treatment.

#### Control group

Participants in the control group may continue to take as usual any IHS guideline-compliant existing symptomatic treatments with analgesics for acute attacks of headache on no more than 10 days per month. For those with chronic tension-type headaches, any pharmacological or non-pharmacological prophylactic treatment compliant with the guideline may also be continued (e.g. amitriptyline or relaxation techniques). After completing the last follow-up assessment 6 months after the initial screening examination, those in the control group will be offered the choice of acupuncture and MTT free of charge over a predefined period of 6 weeks.

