**Methods/design:**

This is a prospective randomized controlled pilot study with four balanced treatment arms (usual care, acupuncture, training, and training plus acupuncture). Each arm will have 24 patients. After the initial screening examination and randomization, a 6-week treatment period follows, with treatment frequencies decreasing at 2-week intervals. After completion of the intervention, two follow-up evaluations will be performed 3 and 6 months after the start of treatment. At predefined times, the various outcomes (pain intensity, health-related quality of life, pain duration, autonomic regulation, and heart rate variability) as well as the participants’ acceptance of the complex treatment will be evaluated with valid assessment instruments (Migraine Disability Assessment, PHQ-D, GAD-7, and SF-12) and a headache diary. The acupuncture treatment will be based on the rules of TCM, comprising a standardized combination of acupuncture points and additional points selected according to individual pain localization. The training therapy comprises a combination of strength training, endurance training, and training to improve flexibility and coordination. Besides descriptive analyses of the samples, their comparability will be assessed using an analysis of variance (ANOVA) or chi-squared tests. Analyses will be performed on an intention-to-treat basis. Potential interaction effects will be calculated using a repeated-measures ANOVA to test the primary and secondary hypotheses. In supplementary analyses, the proportion of treatment responders (those with a 50% reduction in the frequency of pain episodes) will be determined for each treatment arm.

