### Sample size estimation

The sample size calculation was based on the results of Endres et al. [17]. The study was powered to detect a small interaction effect of time × intervention dose (*f* = 0.15) for the primary endpoint (α = 0.05) with a power of 80% in a variance analysis with five repeat measurements and four study groups. With these targets, 20 patients per study group were required for analysis. Assuming a dropout rate of 20% over the course of the trial, 24 patients must be included in each study group; thus, recruitment of 96 participants is required. The sample size calculation was performed using the G*Power 3 software.

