### Patient recruitment

Patients will be invited to participate in the research study by notices in local and regional media and by calls for participation to staff members and students at the Hannover Medical School. Semi-structured telephone interviews and subsequent physical examinations will be performed to select patients with frequent episodic or chronic tension-type headaches according to the diagnostic criteria of the International Classification of Headache Disorders, 3rd Edition (IHS 2.2 and IHS 2.3).

After the telephone screening by two scientific assistants, a potential participant is registered and given an initial appointment, which includes a preliminary medical examination, checking of the inclusion and exclusion criteria, collecting comprehensive information, and providing consent to participate. After this appointment and consent to participate in the study, the subject draws one of the previously created opaque randomization envelopes, is assigned to the corresponding group, and is given dates for appointments for the intervention and for follow-up appointments. The appointments and schedules of the patients enrolled in the study are generated by a study nurse who is neither involved in the treatment nor in the randomization. Randomization will be overseen by one of the trial directors.

The total study period for each participant will be 7 months (Figs. 1 and 2). This period includes a 4-week baseline period, a 6-week intervention period, and a 20-week follow-up period. During the intervention period, the subjects in the trial groups will receive a total of 12 treatment units in decreasing frequency (three units per week during the first 2 weeks, two units per week during the third and fourth weeks, and one unit per week during the last 2 weeks). During the entire study period, as-needed analgesics (e.g. ibuprofen, aspirin, and paracetamol) can be taken as usual and will be documented in a headache diary.

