### Outcome measurements

#### Primary outcome

To test the primary null hypothesis, the change in mean pain intensity (numerical rating scale) before the start of the intervention (T1) compared with the pain intensity 6 weeks after the end of the intervention (T3) is used as the primary endpoint.

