### Trial status

The trial commenced at the beginning of 2018. The approval of the ethics committee was given in June 2018. The recruitment of participants began in July 2018 and was completed in June 2019. The study will be finished in January 2020.

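### The control group's last follow-up is dated from screening but the trial's last follow-up from the start of treatment, so T4 could fall about 4 weeks earlier in usual care

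*Protocol article*

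**What the plan says.** Three places in the protocol article fix the time of the last assessment.

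- **Abstract, Methods/design:** "two follow-up evaluations will be performed 3 and 6 months after the start of treatment". The anchor is the start of treatment.
- **Patient recruitment:** "The total study period for each participant will be 7 months", followed by "This period includes a 4-week baseline period, a 6-week intervention period, and a 20-week follow-up period". No exception is made for any arm.
- **Control group:** "After completing the last follow-up assessment 6 months after the initial screening examination". The anchor is screening. The date appears in the sentence that offers controls acupuncture and training once that assessment is done.

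Three further places decide what depends on this date. The primary outcome is a change from T1, before the intervention, "compared with the pain intensity 6 weeks after the end of the intervention (T3) is used as the primary endpoint". The sample size section assumes a "variance analysis with five repeat measurements and four study groups", and the secondary outcomes section numbers the time points T0 to T4. The statistical analysis section tests the primary hypothesis with a repeated-measures ANOVA for time × intervention and applies the same strategy to the secondary interval-scale outcomes.

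**The concern.** The two anchors lie apart by the time between screening and the start of treatment, and the screening anchor is written for one arm only. That arm is usual care, the comparator in the first part of the primary null hypothesis. Controls receive no study treatment, and the article names no date for them that corresponds to the start of treatment. The control-group sentence is therefore the only timing statement specific to controls.

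A repeated-measures ANOVA treats each time point as the same occasion in every arm. If T4 came at one elapsed time in controls and at a later one in the three active arms, an arm difference at T4 could not be separated from a difference in time since T1. The article also argues, under Limitations, that seasonal effects fall equally on all groups because the arms are evaluated in parallel. Visit timing that differs by arm would weaken that argument at T4.

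**Working it through.** **Inputs.** Baseline 4 weeks, intervention 6 weeks, follow-up 20 weeks, total 7 months (Patient recruitment). Last follow-up 6 months from the start of treatment (Abstract). Last follow-up in controls 6 months from screening (Control group). T3 at 6 weeks after the end of the intervention (Primary outcome). Conversion: 1 month = 365.25 / 12 / 7 = 4.348 weeks.

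**Step 1: reproduce the plan's own schedule.**
- Total: 4 + 6 + 20 = 30 weeks; 30 / 4.348 = 6.90 months. This matches the stated 7 months.
- Start of treatment to the end: 6 + 20 = 26 weeks; 26 / 4.348 = 5.98 months. This matches the 6 months in the abstract.
- Start of treatment to T3: 6 + 6 = 12 weeks; 12 / 4.348 = 2.76 months. This is the follow-up that the abstract rounds to 3 months, so the 6-month visit is T4.

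The abstract and the recruitment section are therefore consistent.

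**Step 2: date T4 under each rule**, with the 4-week baseline taken to run from screening to the start of treatment.

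| | Trial-wide rule | Control-group sentence |
|---|---|---|
| Weeks from screening | 4 + 26.1 = 30.1 | 6 × 4.348 = 26.1 |
| Weeks from T1 | 26.1 | 26.1 − 4 = 22.1 |
| Weeks from end of intervention period | 26.1 − 6 = 20.1 | 22.1 − 6 = 16.1 |

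The difference is 30.1 − 26.1 = 4.0 weeks, the length of the baseline period. As a share of the time after T1 this is 4 / 26 = 15%. That is a share of elapsed time and does not estimate bias.

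**Step 3: the assumption.** In general the gap equals the interval from the initial screening examination to the start of treatment. The article does not say outright that the baseline period begins at that examination. If some of the baseline came before it, the gap would shrink, so the range is 0 to 4 weeks. The 4-week end follows if the 7 months are counted from screening.

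**Step 4: which schedule do the trial dates fit?** Under Trial status, "The recruitment of participants began in July 2018 and was completed in June 2019", with the end of the study given as January 2020. Suppose the last participant was screened between 1 and 30 June 2019.
- Plus 30 weeks: 28 December 2019 to 26 January 2020.
- Plus 26 weeks: 30 November to 29 December 2019.

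The closing date fits 30 weeks. It concerns the last participant in any arm, so it does not show when controls in particular were seen.

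**The case against.** The best case on the other side is that this is a slip in a subordinate clause. The recruitment section gives the 7 months to each participant without exception by arm, a single study nurse prepares all schedules, and the closing date fits 30 weeks. The control-group sentence is about a later treatment offer and mentions the visit date only in passing. The abstract also describes the order of events as "After the initial screening examination and randomization, a 6-week treatment period follows", with no gap mentioned, so the 4 weeks are inferred. The SPIRIT figure, which may show a single anchor, is not available here. All of this stands. It makes a slip likely and limits the weight of the point, but it does not remove the conflict between the stated times.

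A reader might infer two stronger things, and the article supports neither.

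- **Controls could start acupuncture or training before T4.** The control-group sentence places the offer after the last assessment is completed, whatever its date. Treatment before T4 would require departing from that sentence, so no change to the timing of the offer is called for on this ground.
- **The primary endpoint is compromised.** It is the change from T1 to T3, and the control-group sentence re-dates neither. The five measurements are stated as an input to the sample size, and the analysis section does not list which time points enter the primary ANOVA. The primary test is touched only if T4 is one of them.

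**Conclusion.** The inconsistency is real and can be seen from the article alone. One arm's last visit is dated 6 months from screening, while the trial-wide schedule puts it about 7 months from screening. Followed literally, controls would reach T4 about 22 weeks after T1 and the active arms about 26. This rests on the baseline period running from screening to the start of treatment, as the abstract and the recruitment section together imply.

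The reach is limited to comparisons with usual care at T4 and, if all five measurements enter it, the time × intervention test. The T1 to T3 contrast is unaffected. Nothing in the article allows the effect of a 4-week shift on pain scores to be estimated, and none is claimed. The article also does not show that controls were in fact seen early. The likelier explanation is a wording error, which the recorded visit dates can confirm or refute.

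**What to change.** Reconcile the abstract, the Patient recruitment section and the Control group section so that T4 has one anchor in all four arms: the start of the intervention period, or its equivalent date in controls (the end of their baseline period). Before T4 is analysed, tabulate the recorded interval from T1 to T4 by arm. If the arms agree, only the wording needs correcting. If controls cluster near 22 weeks and the others near 26, report this and read the T4 comparisons with usual care accordingly.

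The cost is about one sentence of text and one table from dates already recorded. Sample size, primary endpoint and number of visits do not change.

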### Outcome measurements

#### Primary outcome

To test the primary null hypothesis, the change in mean pain intensity (numerical rating scale) before the start of the intervention (T1) compared with the pain intensity 6 weeks after the end of the intervention (T3) is used as the primary endpoint.

#### Secondary outcomes

One of the secondary endpoints is the frequency of pain episodes in days per month, from which the number of responders (those with at least a 50% pain reduction) and the frequency of occurrence can be calculated.

Other secondary endpoints are the duration of headache attacks, the consumption of pain medication for tension-type headaches, health-related quality of life, effect of headaches on fitness and functional impairments (activities and participation), psychological health (mood, drive, anxiety, etc.), and autonomic factors (sleep–wake patterns). These outcomes will be measured using the Migraine Disability Assessment questionnaire [19], parts of the Patient Health Questionnaire for Depression (PHQ-D) [20], the nine-item Patient Health Questionnaire (PHQ-9) [21], the seven-item Generalized Anxiety Disorder (GAD-7) questionnaire [22], and the 12-item Short Form Health Survey (SF-12) [23]. Because anxiety, in particular, has a significant impact on the expectation of therapy, participants provide a brief written assessment of anxiety prior to each acupuncture treatment, in addition to the standardized assessments of anxiety and depression (PHQ-9 and GAD) -7 T0 to T4) - to evaluate treatment expectations. [24, 25].

At the visit to collect informed consent and at the first medical examination, acupuncture and MTT were presented as equally effective therapies for tension-type headaches to objectify their credibility and the expectations of patients [26]. To evaluate their expectations of the individual therapeutic procedures, they will complete a three-part survey after the intervention phase. On a scale of 0–10 (0 = does not apply, 10 = fully agrees), they will be asked to rate: (1) their expectation of the assigned therapy procedure, (2) whether that expectation was fulfilled, and (3) whether they would recommend the intervention to a relative or friend.

After receiving written and verbal instructions, the patients will independently complete the questionnaires. The completed questionnaires, including their study ID, will be given to the study nurse in a sealed envelope. The outcomes will be entered into a database by a member of the scientific staff who is not involved in the treatment. The data will then be reviewed by two of the principal investigators.

### Safety evaluation

All side effects that occur within the study period will be recorded. These will immediately be reviewed by the study physicians and will be considered in the evaluations. The study physicians will assess the relationship between the intervention and the severity of each adverse reaction. Independent safety monitoring will be provided by a researcher (CE) who is not involved in the study process and works with the university’s independent Medical Process and Patient Safety Unit. Suspected unexpected serious adverse reactions will be reported to the safety unit and the ethics committee. All study participants are covered throughout the trial by insurance. Due to the proven effectiveness of acupuncture and MTT, we consider that a loss of confidence by participants is unlikely. Patients may terminate their participation at any time for any reason. Participants may request a meeting with a study doctor to discuss an alternative treatment. To avoid dropouts, the participants will complete, at several time points, a survey on the organization, processes, possible problems, and their satisfaction with their interactions with the study staff.

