## Methods/design

### Study design

The proposed study is a randomized controlled prospective trial with four balanced treatment arms. It will compare the efficacy of two distinct non-pharmacological treatment modalities (acupuncture vs. MTT), as monotherapies and in combination, with usual care according to IHS criteria for the treatment of common episodic and chronic tension-type headaches. Usual care is the control modality. Subjects will be assigned to one of the four treatment arms (usual care, acupuncture, MTT, and MTT plus acupuncture), using pre-generated randomization lists in a ratio of 1:1:1:1 with varying permutation block sizes. The randomization scheme was prepared by a scientific colleague who is not involved in scheduling, treatment, or evaluation. After the randomization list had been created, written allocation sheets were delivered to the treating physicians in sealed opaque envelopes.

The study is headed by the first and last authors as well as the head of the Departement of Rehabilitation medicine of the Hannover Medical School (CG). Protocol decisions were made in a peer process involving all co-authors. Changes to the study protocol can be made only with the written consent of the ethics committee.

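### The only event class stated to go to the independent safety unit depends on the study team's own attribution, and events are recorded as side effects rather than as adverse events in all arms

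*Protocol article*

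**What the plan says.** Safety evaluation in the Protocol article sets out these steps.

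- Capture: "All side effects that occur within the study period will be recorded".
- First review: "These will immediately be reviewed by the study physicians and will be considered in the evaluations".
- Assessment: "The study physicians will assess the relationship between the intervention and the severity of each adverse reaction".
- Independent oversight: "Independent safety monitoring will be provided by a researcher" who is outside the study process and "works with the university’s independent Medical Process and Patient Safety Unit".
- Onward report: "Suspected unexpected serious adverse reactions will be reported to the safety unit and the ethics committee".

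Three other sections bear on this. Study design says that "written allocation sheets were delivered to the treating physicians in sealed opaque envelopes". Data collection and management adds a second outside person who monitors data, without saying whether safety data are included. The Discussion says that adverse events and their severity will be evaluated, and that this matters for safety and for patients' acceptance of the treatments.

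**The concern.** Independent safety monitoring exists largely to check the study team's own view of what caused an event. Here the one stated report to the safety unit covers a class of events that is partly defined by that view. If the team decides that a serious event was unrelated, or was to be expected, the article states no path by which anyone independent would look at that decision.

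Capture has the same weakness. A side effect is ordinarily something attributed to a treatment; an adverse event is anything untoward, whatever its cause. If recording starts from side effects, attribution comes before the record. The arms differ in what there is to attribute to: needling, training, both, or the participant's existing care. A comparison of harms between arms then partly reflects how readily events were blamed on each treatment.

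At stake are the independence of the safety check and the usefulness of the harms evaluation promised in the Discussion.

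**Working it through.** There is no figure in the plan to reproduce. The check sets the statements side by side.

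**1. Which serious events have a stated route to the unit?** Once an event is serious, two judgements decide whether it belongs to the reported class.

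| Judged related? | Judged unexpected? | Stated report to the safety unit |
|---|---|---|
| yes | yes | yes |
| yes | no | none stated |
| no | yes | none stated |
| no | no | none stated |

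Two judgements with two answers give 2 × 2 = 4 combinations. One has a stated report and 4 − 1 = 3 have none. This counts combinations; it does not say how often each would occur.

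**2. Who makes the judgements?** Safety evaluation assigns the assessment of relationship to the study physicians. It names no second, independent assessor, and it does not say who judges expectedness.

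**3. Are those physicians masked?** The article does not say so. The arms are usual care, needling, training, or both, and the treating physicians received the allocation envelopes. Data collection and management hides allocation on the data sheets from third parties and keeps the acupuncturist, physiotherapists and statisticians from the data during patient evaluations. Neither provision masks the study physicians. That they know the allocation is an inference, though a reasonable one.

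**4. What exactly is assessed?** The assessment sentence joins two items. Read literally, it asks how the intervention relates to the severity of a reaction, and it already calls the event a reaction. Whether the intervention caused the event, and how severe it was, are separate questions. The suspected criterion in the reporting rule needs the first one answered.

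**5. Do the terms match the evaluation that is promised?** Safety evaluation speaks of side effects and adverse reactions; the Discussion speaks of adverse events. The first two presuppose a cause and the third does not. No sentence says that events are sought and recorded on the same basis in all four arms.

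**6. How many reports would the wider rule add?** The documents give no serious-event rate, so the following rates are assumptions. With 4 × 24 = 96 participants:

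- 1%: 96 × 0.01 = 0.96
- 2%: 96 × 0.02 = 1.92
- 5%: 96 × 0.05 = 4.8

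That is about 1 to 5 participants with a serious event in the whole trial, and a similar number of reports at one event each. This figure sizes the workload only; it does not estimate how many events would go unreviewed.

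**The case against.** The strongest objection is that the article does not restrict the monitor. Oversight has its own sentence, with no limit on what the monitor may see. The sentence that follows can be read as an expedited route added to general oversight, since it also names the ethics committee. A second outside person monitors data. The article condenses a fuller protocol, where the monitor's remit, the serious-event listings and the reference for expectedness would normally stand.

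Much of this holds, and it rules out several stronger readings that a reader might infer:

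- *That other serious events never reach the independent monitor.* The text does not say so; the monitor's data scope is open.
- *That usual care has no recorded events by construction.* Control group allows analgesics and, for chronic headache, prophylaxis, so side effects can occur in that arm. The recording sentence is not limited to any arm.
- *That a cardiac event during training would be classed as expected and so not reported.* Eligibility exclusions and the assessment before training ("Based on an initial 45-min physiotherapeutic examination plus a cardiac stress test and testing of strength, endurance, posture control, and flexibility") are screening steps. They do not make such an event expected in those who pass.
- *That the missing reference list for expectedness is an error.* An article may leave this to the full protocol.
- *That presenting both therapies as effective shows biased causality assessment.* Those statements concern patients' expectations and confidence.

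It can also be said that the three terms are used interchangeably. That is plausible, because relationship is assessed after recording. But then the wording does not convey what is meant, and correcting it is simple.

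The objection does not dispose of the reporting sentence. The article chose to state a class for report to the unit, and that class depends on the team's attribution. If the full protocol already sends all serious events there, the printed sentence understates the safeguard.

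**Conclusion.** The point holds in a limited form and the plan should be changed. As written, one class of serious event has a stated report to the independent unit, and entry to it depends on judgements for which no independent assessor is named. Serious events judged unrelated or expected have no stated route to independent review. The record is framed as side effects, which fits poorly with an evaluation of adverse events across four arms.

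This is a weakness in a stated safeguard, not proof that any event was missed or that the monitor was kept from seeing one. It rests on the article alone and on the inference that the study physicians know the allocation. Its effect on the harms comparison cannot be quantified from the documents. It does not touch the primary endpoint, the sample size or the efficacy analysis.

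**What to change.** Amend Safety evaluation in three places.

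1. **Capture.** Record all adverse events in all four arms, whether or not they are thought to be related to an intervention.
2. **Reporting.** Report all serious adverse events in all four arms to the safety unit, whatever their judged relatedness or expectedness. Keep the existing report to the ethics committee.
3. **Assessment.** Rate relatedness to the intervention and severity as two separate items.

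According to Trial status, recruitment ended in June 2019 and the study was to finish in January 2020. The change would therefore apply to the remaining visits, and serious events already on record should be sent to the unit. Non-serious events from past visits cannot be recovered on a uniform basis, so the harms report should say from when the new capture applied.

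The cost is small but not nil. Study design requires the ethics committee's written consent for any change to the protocol. The unit would review a few events that prove unrelated, about 1 to 5 serious-event reports in all under the assumed rates. The change uses the existing safety unit and the remaining visits.
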